### Sample size

The sample size was obtained using
G*Power 3.0.10 software, based on the outcomes from a pilot study. The calculation was carried out by the two-way repeated measures analysis of variance (ANOVA), considering the mean value (before and after training, and 30-day follow-up) for the control groups (25.46) active (27.46) and sham (24.66) and the pooled standard deviation (SD
_pooled_) (2.89), with α = 0.05, β = 0.2 (80% of power) and the effect size of 0.40. A total of 15 individuals were determined to be required for each group (total sample: 45 individuals). Considering possible dropouts and to ensure a sample size that will demonstrate the effect of the intervention, the sample will be expanded by 25%, resulting in 19 individuals in each group, thus totalling 54 participants.

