### Intervention procedures

***Video game Balance training***. The balance training sessions will be performed using only the video games in group 1 (control), group 2 will be the balance training with the video games associated with the anodal tDCS and group 3 will be the balance training with the video games associated with the sham tDCS. In this study, a control group was added that performed the same training as the other groups. However, using only the video game. The justification for this was to verify if only the balance training with video game is efficient and if the tDCS additional can potentiate the training results, making the outcomes more effective. The sham group was used to verify if the response to balance training with video game, can be influenced by some placebo effect.

Video game training will be carried out with the Nintendo Wii and Wii Fit Plus, placed in a slide projector to enlarge the image. The sequence of games will always be the same, and the participant should play an average of 5 to 7 minutes each game, passing the stage according to their learning.

The sessions will be held twice a week, for four weeks, totalling eight sessions. Each session will last 20 minutes. The selected games are table tilt, penguin slide and ski slalom, which will be performed standing on the Wii Board Balance and require movements that stimulate balance, such as the anterior, posterior and lateral tilt of the body, without moving (
Figure 1).

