### Blinding

The NeuroConn DC-STIMULATOR PLUS device has settings that allow the selection of the anodal stimulation or sham mode, by inserting codes. A researcher not involved in the procedures will program the equipment with the code to which the individual will be allocated. The stimulus mode will not be perceived by the external (supplementary functioning of the device, therefore, neither the researcher who will apply the intervention nor the individual will know what treatment will be applied (double-blind).

Participants in the group that will only perform training with video game will not be blind to treatment; however, a researcher will be responsible for the exclusive training of this group and will not be aware of the procedures with the tDCS of the other groups. All assessments will be made by researchers who have not participated in the training of the older people, and will, therefore, be blind to the intervention. A blinding questionnaire will be applied to guarantee its reliability and satisfaction with the treatment received (supplementary files 3 and 4), without the researcher knowing the training carried out by the participant.

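### Sham v games-only is given the job of showing a placebo effect, but the games-only arm has its own trainer, so neither a difference nor its absence can be attributed to placebo

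*Protocol article*

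**What the plan says.** Three places in the Protocol article bear on this.

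- **Intervention procedures** gives the reason for the third arm: "The sham group was used to verify if the response to balance training with video game, can be influenced by some placebo effect". It gives the games-only arm a separate purpose: to see whether game training works alone and whether adding tDCS strengthens it.
- **Blinding** states that participants in the games-only group know their treatment and that "a researcher will be responsible for the exclusive training of this group". That trainer is kept unaware of the tDCS procedures in the other groups. In the anodal and sham groups the stimulation mode is set by a device code, so neither the participant nor the person delivering the session knows it. Outcome assessors take no part in training.
- **Sample size** sizes the trial on a three-group repeated measures ANOVA, using pilot means "for the control groups (25.46) active (27.46) and sham (24.66"), a pooled SD of 2.89 and "the effect size of 0.40". It gives no power and no expected effect for sham against games-only.

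The hypothesis at the end of the Introduction compares games plus tDCS with games alone.

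**The concern.** A placebo influence on the training response can be seen only by comparing sham plus games with games alone. For that comparison to isolate expectation and the sham procedure, the two arms should otherwise be run alike. They are not, because one trainer is tied to the games-only arm. A more or less encouraging trainer there could produce an apparent placebo effect or cancel a real one.

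The consequence reaches beyond the sham arm's rationale. If sham and games-only do not differ significantly, a reader could take placebo as ruled out and then treat anodal minus games-only as a pure tDCS effect. If they do differ, the difference could be reported as placebo when it is a trainer effect. The design supports neither step.

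**Working it through.** **1. What each contrast contains.** This follows from the Intervention procedures and Blinding sections.

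| Contrast | Active current | Expectation and electrode procedure | Trainer differs by design |
|---|---|---|---|
| Anodal minus sham | yes | no (same procedure, mode hidden) | no |
| Sham minus games-only | no, apart from the 30 seconds of sham current | yes | yes |
| Anodal minus games-only | yes | yes | yes |

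The trainer of the games-only arm is constant within that arm and absent from the other two. Trainer is therefore fully aliased with arm in the last two rows, and no larger sample or different model separates it. That games-only participants know they receive no stimulation is inherent in any placebo comparison. The separate trainer is not.

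**2. The plan's own sample size.** Inputs from Sample size: means 25.46, 27.46 and 24.66; SD 2.89; alpha 0.05; power 80%.

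- The grand mean is 25.86 and the SD of the three means about it is 1.178, so f = 1.178/2.89 = 0.407. This agrees with the stated 0.40.
- For the between-groups test over 3 visits, lambda = N × 3 × f² / (1 + 2ρ). With f = 0.40, ρ = 0.5 (assumed; the document gives no correlation) and N = 45, lambda = 45 × 3 × 0.16 / 2 = 10.8. Power on 2 and 42 degrees of freedom is 81.7%. At N = 42 it is 78.6%.

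The stated 15 per group is thus reproduced, for the three-group test only.

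**3. Precision of sham minus games-only.** Half-width = t(0.975, 2n − 2) × SD × √(2/n). The section gives 15 per group before dropout, and after inflation 19 per group but 54 in total (18 per group), so all three are shown.

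| n per arm | t | Half-width, one visit, SD 2.89 |
|---|---|---|
| 15 | 2.048 | 2.16 |
| 18 | 2.032 | 1.96 |
| 19 | 2.028 | 1.90 |

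**4. On change from baseline.** SD of change = 2.89 × √(2(1 − ρ)). The correlation ρ is not given, so a range is shown.

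| ρ (assumed) | SD of change | Half-width, n = 15 | n = 18 | n = 19 | Power for 2.0 points, n = 15 to 19 |
|---|---|---|---|---|---|
| 0.3 | 3.42 | 2.56 | 2.32 | 2.25 | 34% to 42% |
| 0.5 | 2.89 | 2.16 | 1.96 | 1.90 | 45% to 55% |
| 0.8 | 1.83 | 1.37 | 1.24 | 1.20 | 82% to 91% |

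The 2.0 points is a yardstick only: it is the pilot gap between anodal and games-only, 27.46 − 25.46. At ρ of 0.3 or 0.5, an interval centred on zero would reach or nearly reach it (half-widths 1.9 to 2.6). Even at ρ = 0.8, differences of more than a point in either direction would remain compatible with a null result.

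**The case against.** **The sentence explains why an arm exists; it is not an objective.** The Introduction's objectives do not mention placebo, and a trial need not be powered for every rationale it gives. That is fair, and it is why lack of power is not the main point here. The trainer confounding does not depend on power, and it also affects the comparison in the stated hypothesis.

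**The trainer's influence may be small.** The game sequence is fixed and assessors are separate from training, which limits the trainer's effect without removing it. Keeping that trainer away from the tDCS procedures was also a deliberate choice.

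**Stronger readings that the document does not support:**

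- A reader might infer that the plan gives this contrast only 11% to 13% power. A two-sided t-test for 25.46 − 24.66 = 0.80 points with SD 2.89 does give 11.3% at 15 per arm and 13.2% at 19. But 0.80 is a pilot gap with sham *below* games-only, opposite to a placebo benefit, and the averaged means appear to include the pre-training visit. The plan never puts it forward as a placebo effect. For 2.0 points on change scores, power runs from 34% to 91% over the correlations shown.
- A reader might infer that the sham arm's purpose cannot be met at all. The difference can be estimated with an interval; it cannot be attributed to placebo alone.
- A reader might infer that a null result will be reported as no placebo effect. The article gives no rule for reading a null result, so this is a risk and not something the plan states.
- A reader might infer from Statistical analysis that this contrast will not be tested. A three-group ANOVA does not preclude follow-up contrasts, which may be set out in an analysis plan not shown here.

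**Conclusion.** The concern holds as a problem of attribution, with imprecision as a second limit. Because the games-only arm has an exclusive trainer, sham minus games-only combines expectation, electrode procedure and trainer. Neither a difference nor its absence can be put down to placebo. Anodal minus games-only carries the same trainer confounding. Anodal minus sham, the blinded test of tDCS, is unaffected.

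The 95% confidence interval for sham minus games-only would extend about 1.9 to 2.2 points either side at one visit, and about 1.2 to 2.6 on change scores. These figures assume that the pilot SD of 2.89 applies in the trial, that 15 to 19 participants per arm are analysed, and that the between-visit correlation lies between 0.3 and 0.8. A non-significant result would not show absence of a placebo effect. The size and direction of any trainer effect are unknown. The point should be corrected because it governs what the trial may conclude.

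**What to change.** - **Reword the rationale in Intervention procedures.** Say that sham is the comparator for the tDCS-specific effect, estimated by anodal minus sham.
- **Report both comparisons with games-only** (sham minus games-only and anodal minus games-only) as mean differences with 95% confidence intervals. Describe them as including sham procedure, expectation and trainer, the second also including the active current. Draw no conclusion that a placebo effect is present or absent.
- **Optional: share trainers across arms for participants not yet enrolled.** The device code would still hide anodal from sham. Trial status says collection is already under way, so this would reduce the confounding and not remove it. It would also make the trainer mix vary over calendar time and give up the deliberate separation of the games-only trainer, so it should be documented if done.

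The first two changes cost a rewritten sentence and two estimates from data already being collected. The downside is that the trial gives up a claim about placebo effects.

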### tDCS

tDCS will be performed with a tDCS device, the NeuroConn DC_STIMULATOR PLUS, from Germany, by means of two non-metallic surface electrodes, cathode 35 cm
^2^ (5 × 7 cm) and anode 25 cm
^2^ (5 × 5 cm), both wrapped in sponges moistened in a saline solution.

The intensity will be 2mA with a 20-second ramp up and down for a 20-minute period of stimulation. The montage will be anodal, unbalanced bilateral bipolar, anode positioned over the dorsolateral prefrontal cortex of the dominant hemisphere (F3 or F4) and the cathode electrode on the supraorbital region contralateral to the anode (
Figure 2), according to the criteria of the 10–20 electroencephalogram system
^27^. The application of the sham tDCS will occur in the same way, with the electrodes in the same positions as the anodal tDCS group, keeping working for 30 seconds.

**Figure 2. f2:**
[figure not shown]
Positioning the participant on the board for the execution of the therapy with
*Nintendo Wii* associated with active stimulation or sham. Source: author’s own, consent received for publication.

### Assessment of the potential adverse effects

At the end of each session, a questionnaire on the adverse effects of tDCS will be applied to the participant
^24^ (see Extended data, Assessment of tDCS Adverse Events form).

### Blinding

The NeuroConn DC-STIMULATOR PLUS device has settings that allow the selection of the anodal stimulation or sham mode, by inserting codes. A researcher not involved in the procedures will program the equipment with the code to which the individual will be allocated. The stimulus mode will not be perceived by the external (supplementary functioning of the device, therefore, neither the researcher who will apply the intervention nor the individual will know what treatment will be applied (double-blind).

Participants in the group that will only perform training with video game will not be blind to treatment; however, a researcher will be responsible for the exclusive training of this group and will not be aware of the procedures with the tDCS of the other groups. All assessments will be made by researchers who have not participated in the training of the older people, and will, therefore, be blind to the intervention. A blinding questionnaire will be applied to guarantee its reliability and satisfaction with the treatment received (supplementary files 3 and 4), without the researcher knowing the training carried out by the participant.

### Statistical analysis

All statistical tests will be performed using
SPSS (V22, IBM Corporation, New York, USA). Initially, we will perform the test of normality of the sample using the Shapiro-Wilk test, considering the significance level defined as a value of α < 0.05. The parametric data will be expressed as a mean ± SD (standard deviation), and the nonparametric data as a median (IQR); the categorical data will be described as absolute values and as a percentage of the total sample.

The variables of the data of the Mini-BESTest, Posturography, obtained pre-intervention, post-intervention and 30-day follow-up for the three groups (control, active and sham) will be calculated by the two-way repeated measures analysis of variance (ANOVA) for the parametric data and the Friedman’s test for the nonparametric data.

Finally, to verify whether there is a correlation between BESTest values and the symptoms of depression and quality of life, Pearson’s R correlation (parametric) or Spearman correlation (nonparametric) for the three groups in three evaluated times will be performed, verifying the degree of correlation (r) and its significance (p).

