18^, therefore, further studies are necessary to verify the benefit of tCDS in association with other therapies. For that reason, the primary objective of this study is to assess whether tDCS can enhance and prolong the effects of videogame training on improving postural balance in the older people. Secondarily, check if there is a relationship between the response to training and the quality of life. This study hypothesizes that the association of tDCS with virtual reality therapy is more effective in improving balance in the older people than therapy with videogames alone, and that the addition of tDCS will prolong the effects of balance training.

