### Outcome assessments

All evaluations will be carried out on three occasions: pre-intervention, after eight treatment sessions and 30 days after the end of the training (follow-up). The training will be held twice a week, for 4 weeks, totalling 8 sessions.

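### The plan does not say which effect or visit decides the Mini-BESTest result, and its sample size and its hypothesis point to different tests; if either group-related F test counts, the false-positive rate is about 10%, not 5%

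*Protocol article*

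**What the plan says.** The Primary outcomes section names the Mini-BESTest, and Outcome assessments sets the visits: "All evaluations will be carried out on three occasions: pre-intervention, after eight treatment sessions and 30 days after the end of the training (follow-up". Under Statistical analysis, the Mini-BESTest and posturography data from the three groups and three visits "will be calculated by the two-way repeated measures analysis of variance (ANOVA) for the parametric data", with "the Friedman’s test for the nonparametric data" as the alternative. No model term, pairwise contrast or visit is singled out. The only significance level in that section is in the sentence on the normality test: "considering the significance level defined as a value of α < 0.05".

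Two other sections bear on which test is meant:

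- **Sample size** works from one mean per group, "considering the mean value (before and after training, and 30-day follow-up"), namely "for the control groups (25.46) active (27.46) and sham (24.66"), "with α = 0.05, β = 0.2 (80% of power) and the effect size of 0.40".
- **Introduction** hypothesises that tDCS with video games improves balance more than video games alone, and that "the addition of tDCS will prolong the effects of balance training".

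**The concern.** A 3 × 3 repeated-measures ANOVA gives two F tests that involve group. The group main effect compares levels averaged over all visits, baseline included. Group × time asks whether the groups change differently. The sample size relies on the first, while both parts of the hypothesis are about change from baseline, which the first does not isolate. The analysis section does not choose between them.

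Two things are at stake. If a significant result on either test would be reported as success, the 5% level does not hold for the trial's claim. And if the treatment works, the two tests will often give different answers, so the conclusion would rest on a choice that can be made after the data are seen.

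**Working it through.** **Inputs.** From Sample size: means 25.46 (control), 27.46 (active), 24.66 (sham); pooled SD 2.89; α = 0.05; power 0.80; f = 0.40; 15 per group, N = 45. There are m = 3 visits. The correlation between visits is not stated. I assume ρ = 0.5 and vary it.

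**Step 1. Which test do the 45 participants belong to?**

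- Grand mean = (25.46 + 27.46 + 24.66)/3 = 25.86. The deviations are −0.40, 1.60 and −1.20.
- f = √[(0.16 + 2.56 + 1.44)/3] / 2.89 = 1.178/2.89 = 0.407, which agrees with the stated 0.40.
- Group main effect: λ = N·f²·m/[1 + (m−1)ρ] = 45 × 0.16 × 3/2 = 10.8, with 2 and 42 df. Power is 81.7%. At N = 42 it is 78.6%, so 45 is the smallest balanced total that reaches 80%.
- Group × time, same inputs: λ = N·f²·m/(1−ρ) = 45 × 0.16 × 3/0.5 = 43.2, with 4 and 84 df. Power is above 99.9%, and 18 participants would be enough.
- A one-way ANOVA at a single visit would need 66.

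So 45 reproduces as the group main effect averaged over the three visits, baseline included.

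**Step 2. False-positive rate with no effect in any group.** The F tests below use simulated 3 × 3 data (40,000 trials per setting, 15 per group, equal correlation between visits, ρ from 0 to 0.9). The contrasts are two-sided t tests on change from baseline.

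| What counts as success | Rate |
|---|---|
| One F test named in advance | about 5% |
| Either group or group × time at 0.05 | 9.5–9.8% |
| Anodal v games alone, at either later visit | about 9% |
| Anodal v games alone and v sham, at either later visit, no adjustment | 16–17% |
| The same four contrasts, only after a significant group or group × time F | just under 5% |

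As a check on the second row, two independent tests give 1 − 0.95² = 9.75%.

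**Step 3. How often the two F tests disagree when tDCS works.** Suppose a true 2-point anodal gain at both later visits and none in the other groups, SD 2.89 (variance 8.352), 15 per group.

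- Averaged over three visits the gain is 4/3. For the group effect, λ = 15 × (2/3) × (4/3)² / [8.352 × (1 + 2ρ)/3].
- For group × time, the squared deviations of (0, 2, 2) from their mean sum to 8/3, so λ = 15 × (2/3) × (8/3) / [8.352 × (1 − ρ)].

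| ρ | λ group | Power, group | λ group × time | Power, group × time | Disagree |
|---|---|---|---|---|---|
| 0.5 | 3.19 | 32% | 6.39 | 47% | 49% |
| 0.84 | 2.38 | 25% | 19.96 | 95% | 73% |

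The two tests are independent under this model, so the disagreement rate is p₁(1 − p₂) + p₂(1 − p₁). At ρ = 0.5 that is 0.319 × 0.527 + 0.473 × 0.681 = 0.49. At ρ = 0.84 it is 0.247 × 0.047 + 0.953 × 0.753 = 0.73. Simulation gives the same figures.

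**The case against.** The strongest reply is about scope. Only a journal article is shown, and the choice of model term, the post hoc contrasts and their adjustment are commonly left to a full protocol or SAP. Had the article merely been silent, that would settle the matter. It is not silent: Sample size points to one test and the Introduction to another. A later document could resolve this, but only by departing from one of those two sections.

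The other objections limit how far the point goes:

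- A reader might infer that every test is declared at the full 5%. The article does not say so. The 0.05 appears as a sample-size input and in the normality-test sentence. That no adjustment applies is an inference from silence.
- A reader might take 16–17% as the trial's error rate. That figure needs four unadjusted contrasts, and the article plans no pairwise tests. The hypothesis names only games alone as comparator; sham is described, under Intervention procedures, as a check on placebo effect.
- If both parts of the hypothesis had to succeed before a claim was made, the false-positive rate would be at most 5%. The 9% applies only if either part alone would be claimed.
- A reader might add posturography to the family and obtain a higher rate. It is already labelled secondary, so it does not belong in the primary claim.
- The disagreement figures arise under a true effect. They reflect the different power of the two tests and are not false positives.
- All the rates describe the ANOVA branch. Friedman's test compares visits within participants and has no between-group test, so they do not carry over to it.

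**Conclusion.** The concern holds in a limited form. The analysis section does not name what decides the primary outcome, and the article's own sections point to two tests that answer different questions. If a significant result on either group-related F test counts as success, the false-positive rate is about 10%, twice the 5% used in the design. It is about 9% if either claim against games alone counts. It reaches 16–17% only under unadjusted comparison with both other groups at both later visits. With one test named in advance it is 5%.

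The 10% hardly depends on the visit correlation. The 49–73% disagreement does: it assumes ρ of 0.5 to 0.84, a 2-point gain sustained to 30 days, equal correlation between visits and 15 analysed per group. The false-positive rates depend on how the results would be read, which the article leaves open. They do not show that the sponsor intends to claim success on any one of several tests.

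**What to change.** Amend the Statistical analysis section before unblinding:

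1. Name one deciding test for Mini-BESTest: a baseline-adjusted between-group contrast at the post-training visit, at a two-sided 5% level. The sponsor should choose the comparator in line with its hypothesis, which at present names games alone.
2. Test the same contrast at 30 days only if the first is significant. This gives the claim of a prolonged effect a defined place at no cost in alpha.
3. Put the remaining comparator next in the order, or label it supportive.
4. State that the ANOVA group main effect, which includes baseline, and the time effect support no efficacy claim.

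The sample-size text should then refer to the deciding test. If both F tests were kept instead, testing each at 0.025 would hold the total to at most 5%, but it would still not say which one answers the hypothesis.

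The cost is a change of wording, with no extra participants or data. The small downside is that later contrasts cannot be claimed if the first one fails.

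### The repeated-measures ANOVA treats the pre-training score as an outcome; adjusting for it as a covariate would be more precise with the same data, by an amount that depends on an unstated correlation

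*Protocol article*

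**What the plan says.** The Statistical analysis section of the protocol article takes the Mini-BESTest and posturography values "obtained pre-intervention, post-intervention and 30-day follow-up for the three groups (control, active and sham" and states that they "will be calculated by the two-way repeated measures analysis of variance (ANOVA". Friedman's test replaces the ANOVA where the Shapiro-Wilk test rejects normality. The software is "SPSS (V22, IBM Corporation, New York, USA". No baseline covariate is mentioned. Quality of life appears in this section only in correlations.

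The section on outcome assessments fixes the visits: "All evaluations will be carried out on three occasions: pre-intervention, after eight treatment sessions and 30 days after the end of the training (follow-up". There are thus one baseline and two post-training values per participant, and all three are levels of the repeated factor.

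The Sample size section uses the same structure, "considering the mean value (before and after training, and 30-day follow-up) for the control groups (25.46) active (27.46) and sham (24.66", with a pooled SD of 2.89, and works "with α = 0.05, β = 0.2 (80% of power) and the effect size of 0.40". This gives 15 per group. The sample is then enlarged by 25%: "Considering possible dropouts and to ensure a sample size that will demonstrate the effect of the intervention". The section gives 19 per group but a total of 54, whereas 3 × 19 = 57.

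**The concern.** Before training, randomised arms differ only by chance. A test that counts the pre-training score as a response either averages in a visit at which no treatment effect can exist (group main effect) or subtracts the baseline in full (group by time). Full subtraction is efficient only when r is close to 1. At lower values it adds baseline noise to the contrast and over-corrects for chance imbalance, which is not negligible in arms of 18 or 19.

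The aim is to show that stimulation both enhances and prolongs the effect of training. That calls for arm differences at the end of training and at 30 days, estimated as precisely as the data allow.

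A smaller matter is that the standard repeated-measures ANOVA procedure needs every level of the repeated factor. Someone assessed at baseline and after session 8 but not at 30 days would also leave the end-of-training comparison.

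**Working it through.** **1. The plan's own figure.** The group means 25.46, 27.46 and 24.66 have mean 25.86 and SD (divisor 3) 1.178, so f = 1.178/2.89 = 0.407, stated as 0.40. For the between-group effect over m = 3 visits, λ = f²·N·m/(1+(m−1)ρ) with 2 and N−3 degrees of freedom. With ρ = 0.5 (assumed):
- N = 45: λ = 0.16·45·3/2 = 10.8, power 0.817.
- N = 42: λ = 10.08, power 0.786.

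The stated 45 is therefore reproduced as the group main effect averaged over all visits, baseline included. At the same f and ρ the group-by-time interaction would need 18, and a one-way ANOVA 66.

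**2. Dilution in the main effect.** If the arms are equal at baseline and differ by d at both later visits, the averaged difference is (0 + d + d)/3 = 2d/3.

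**3. Change score against baseline adjustment.** With equal variances σ² and correlation r, the variance factors for one post-training visit are:
- change score: 2(1−r)
- baseline-adjusted: 1−r²
- ratio: (1+r)/2

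For the mean of two post-training visits under equal correlations, the factors are 1.5(1−r) and (1+r)/2 − r². Their ratio is 0.53, 0.67 and 0.80 at r = 0.3, 0.5 and 0.7.

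**4. Power, two arms, one visit.** Inputs from the Sample size section are 15 per group, SD 2.89 and two-sided α 0.05. The differences are 27.46 − 24.66 = 2.8 (active minus sham) and 27.46 − 25.46 = 2.0 (active minus control). They are gaps between means averaged over all visits, used here as illustrative post-training differences. SE = 2.89·√factor·√(2/15), with power from the noncentral t on 28 df. At r = 0.5, SE = 1.055 for the change score and 0.914 adjusted.

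| r (assumed) | variance ratio | 2.8 points: change v adjusted | 2.0 points: change v adjusted |
|---|---|---|---|
| 0.3 | 0.65 | 58% v 77% | 34% v 48% |
| 0.5 | 0.75 | 73% v 84% | 45% v 56% |
| 0.7 | 0.85 | 91% v 95% | 66% v 73% |
| 0.84 | 0.92 | 99.5% v 99.7% | 90% v 92% |

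Taking one degree of freedom for the covariate lowers the adjusted figures by about 0.1 point.

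**5. Three arms, simulated.** Inputs: N = 54, post-training shifts 0, +2.0 and −0.8, equal baselines, r = 0.5, 2,500 runs. The adjusted analysis tested the group effect averaged over the post-training visits.
- No dropout: 56% (ANOVA main effect), 78% (group by time), 96% (baseline-adjusted).
- 20% random loss, half of it before the end-of-training visit: 48%, 66% and 92%.

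In the second case the adjusted analysis on completers alone already had 90%, so keeping partial completers added about 2 points. Participants used were about 43 in the ANOVA and 49 in the adjusted model. Part of the advantage over group by time comes from testing 2 rather than 4 degrees of freedom.

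**6. Size of the missing-visit point.** 15 × 1.25 = 18.75, rounded to 19. The loss that returns 19 to 15 is 4/19 = 21%; without rounding it is 1 − 1/1.25 = 20%. That is 57 − 45 = 12 participants, or 54 − 45 = 9 on the stated total. These are upper limits, reached only if all of them attend the end-of-training visit and miss the 30-day one.

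**The case against.** **The gain depends on an assumed r.** This stands. The article gives no pre-post correlation, and at r = 0.84 the gain nearly vanishes. That value equals the Mini-BESTest ICC quoted under Primary outcomes, but an ICC describes reliability and is not a pre-post correlation under training. Entry limited to scores of 25 or less narrows the baseline range and tends to lower r. Neither end of the range can be excluded, but adjustment was ahead at every value tried.

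**The power table is not the planned test.** This also stands. It is a two-arm, single-visit calculation. The three-arm simulation points the same way but rests on its own assumptions about shifts and dropout.

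**Missing-data rules may sit in an analysis plan not shown.** This is fair. The article mentions neither deletion nor imputation, so dropping incomplete cases is inferred from how the standard procedure works. The use of baseline as an outcome, however, is fixed in the text.

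**Stronger readings.** A reader might take the 25% as the expected dropout rate and conclude that about 14 of 57 will be discarded. The 25% is an expansion factor and implies 20 to 21% loss; the text speaks only of possible dropouts and gives no timing. A reader might also infer that the ANOVA is invalid or the result biased. Under loss unrelated to outcome it is valid, and the article gives no information on reasons for dropout. Nor would a mixed model keep everyone randomised.

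**Conclusion.** The point holds as one of efficiency. The article fixes an analysis with the pre-training score as an outcome level. Of its two group tests, one dilutes a constant post-training effect to two thirds and the other is in effect a change-score comparison with variance larger by a factor 2/(1+r) at a single visit. For 2.8 points the power given up runs from about 18 points at r = 0.3 to 0.2 at r = 0.84; for 2.0 points, from about 14 to about 2.

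These figures assume that 2.89 is the SD at one visit, that variances are equal across visits, and that the pilot gaps can serve as post-training differences. Case deletion is secondary: at most about 12 of 57 (9 on a total of 54) would be needlessly excluded from the end-of-training comparison, and fewer if some leave earlier. The change should be made, but the planned ANOVA does not invalidate the trial.

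**What to change.** For Mini-BESTest and posturography, replace the ANOVA by a linear mixed model (MIXED in SPSS) on the two post-training visits, with baseline score as covariate, group, visit, group by visit and an unstructured covariance. Include every randomised participant with at least one post-training score, in the allocated group. Report arm differences with 95% confidence intervals at each visit. A small-sample degrees-of-freedom correction is advisable with about 18 per arm.

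State that this is the analysis regardless of the Shapiro-Wilk result. Otherwise the Friedman branch remains and the model may never be used. Leave quality of life as planned, since a between-arm comparison there would be an addition.

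Cost: no extra participants, visits or software. The model spends one degree of freedom and assumes data are missing at random, which is weaker than what the completer ANOVA needs. Participants with no post-training score are still not recovered. Because data collection is under way and the sample was sized on the ANOVA, the change belongs in a dated amendment before unblinding.
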